## Abstract

**Background:**

Transcutaneous electric acupoint stimulation (TEAS) has shown benefits when used peri-operatively. However, the role of numbers of areas with acupoint stimulation is still unclear. Therefore, we report the protocol of a randomized controlled trial of using TEAS in elderly patients subjected to gastrointestinal surgery, and comparing dual-acupoint and single-acupoint stimulation.

**Methods/design:**

A multicenter, randomized, controlled, three-arm design, large-scale trial is currently undergoing in four hospitals in China. Three hundred and forty-five participants are randomly assigned to three groups in a 1:1:1 ratio, receiving dual-acupoint TEAS, single-acupoint TEAS, and no stimulation, respectively. The primary outcome is incidence of pulmonary complications at 30 days after surgery. The secondary outcomes include the incidence of pulmonary complications at 3 days after surgery; the all-cause mortality within 30 days and 1 year after surgery; admission to the intensive care unit (ICU) and length of ICU stay within 30 days after surgery; the length of postoperative hospital stay; and medical costs during hospitalization after surgery.

**Discussion:**

The result of this trial (which will be available in September 2019) will confirm whether TEAS before and during anesthesia could alleviate the postoperative pulmonary complications after gastrointestinal surgery in elderly patients, and whether dual-acupoint stimulation is more effective than single-acupoint stimulation.

**Trials registrations:**

ClinicalTrials.gov, ID: NCT03230045. Registered on 10 July 2017.

**Electronic supplementary material:**

The online version of this article (10.1186/s13063-018-3052-2) contains supplementary material, which is available to authorized users.

## Background

Life expectancy has been increasing in recent years. In parallel with the increase of life expectancy, the number of elderly patients undergoing surgery is rising. Some of the diseases, such as gastrointestinal cancers, are predominant diseases of this elderly population and the major causes of morbidity and mortality. It had been reported that more than 30% patients with gastric cancer were older than 70 years [1]. Age exceeding 70 years is an independent predictor of increased postoperative complications, in-hospital mortality, and longer hospital stays [2]. Among the postoperative complications, pulmonary complications are closely related to general anesthesia. Atelectasis develops within minutes after the induction of general anesthesia [3] and age is a risk factor of pulmonary complications. Almost all mechanically ventilated, elderly patients developed atelectasis and shunting during anesthesia [4].

Acupuncture is an integral part of an ancient Chinese system of medicine that has been used for more than 2500 years to treat diseases and relieve pain. The use of acupuncture during anesthesia, which is called anesthesia-assisted-anesthesia, is promising in three aspects [5–7]: decreasing the need for anesthetics such as opioids, alleviating adverse events, and exerting organ-protective effects. Electrical stimulation of acupoints, which includes electroacupuncture and transcutaneous electric acupoint stimulation (TEAS), was developed as an alternative to manual acupuncture. Electrical stimulation has several advantages over manual stimulation, such as causing less pain, being less time consuming, and with better standardization.

However, whether the more acupoints stimulated the better the benefit is still in debate. Though according to the Traditional Chinese Medicine (TCM) theory, combinative stimulation of acupoints is important, some investigators found that there was no difference between dual-acupoint and single-acupoint stimulation [8]. In this study, we hypothesize that TEAS before and during surgery would decrease the morbidity or mortality of major postoperative pulmonary complications at 30 days after gastrointestinal surgery in elderly patients, and dual-acupoint stimulation would be better than single-acupoint stimulation.

## Methods/design

### Ethical issues

The sponsor is responsible for the study. The study will be conducted in accordance with the protocol, applicable regulatory requirements and the ethical principles of the Declaration of Helsinki as adopted by the 18th World Medical Assembly in Helsinki, Finland, in 1964 and subsequent versions. The study protocol and statistical analysis plan have been approved for all centers by a central ethics committee (Ethics Committee, Xijing Hospital, Fourth Military Medical University, Xi’an, Shaanxi, China) (No. 20162019-X-1) according to Chinese law. The study has been registered at ClinicalTrials.gov (NCT03230045). All patients should give written informed consent prior to entering the study. The investigator should inform the patients of the protocol, objective and possible risks of the study. And the patients should be assured that they could quit the study any time.

### Design

We adhered to the Standard Protocol Items: Recommendations for Interventional Trials (SPIRIT) guidelines in the preparation of this protocol (see Fig. 1 and Additional file 1 for the SPIRIT Figure and Checklist, respectively). The trial is an investigator-initiated, multicenter, randomized clinical trial comparing treatment with dual-acupoint TEAS versus single-acupoint stimulation and no-stimulation before and during anesthesia in elderly patients undergoing gastrointestinal surgery. Three hundred and forty-five participants will be included from the following four hospitals: First Affiliated Hospital of Fourth Military Medical University (Xijing Hospital); Second Affiliated Hospital of Guangzhou University of TCM; First Affiliated Hospital of Chongqing Medical University; and First Affiliated Hospital of Zhengzhou University. These participants will be randomly assigned to three groups through central randomization in a 1:1:1 ratio. The central randomization system will be used and performed by the Department of Anesthesiology of Xijing Hospital. In each center, an investigator who is not involved in anesthesia and follow-up will perform the randomization. This investigator logs into the central randomization system and inputs the patient’s information, then a random number and group assignment will be immediately given by the system. According to the assignment, the patients will receive interventions from 30 min before anesthesia induction to the end of the surgery. The follow-up period lasts for 1 year. Outcomes are assessed at baseline and 1, 3, and 30 days, and 1 year after surgery.

**Fig. 1 Fig1:**
[figure not shown]
Standard Protocol Items: Recommendations for Interventional Trials (SPIRIT) Figure. Interventions and assessments will be administered at different time points (indicated by X). See description within the manuscript for more details. *TEAS* transcutaneous electric acupoint stimulation

### Patients

#### Study population

The study focuses on patients aged 65 years or older who were scheduled for elective gastrointestinal surgery under general anesthesia.

#### Inclusion criteria

Participants will be included if they fulfill the following conditions: scheduled for elective gastrointestinal surgery under general anesthesia; aged 65 years or older; provided a signed written consent form.

#### Exclusion criteria

Patients with any of the following conditions will be excluded: contraindications to the use of electroacupuncture (including those with infection or injury of the skin to attach electrodes, and those with implanted electronic devices); difficulty in communication; surgery within 12 h of admission to hospital; preoperative pneumonia or on ventilator; history of lung surgery; surgery involving thoracic manipulation; being involved in other clinical trials in the last 3 months.

### Interventions and comparison

#### Rationale for acupuncture protocol

On the day before surgery, patients are randomly assigned to the dual-acupoint TEAS group (DT), the single-acupoint TEAS group (ST) or the Control group, stratified by study center with a central computer-generated scheme. For all the patients, the electrodes (5 × 5 mm^2^) are placed at bilateral ST36 (*Zusanli*) and BL13 (*Feishu*), and then connected to the Hwato Electric Acupuncture Treatment Instrument (model No. SDZ-V; Suzhou Medical Appliances Co, Ltd., Suzhou, China). Thirty minutes before surgery, the intervention is performed by an investigator who is not involved in anesthesia and follow-up. For group DT, ST36 and BL13 are stimulated. For group ST, only ST36 is stimulated. For the Control group, electrodes are attached but no stimulation is given.

ST36 and BL13 are chosen and identified according to ancient Chinese medical books. ST36 is the most often used acupoint for abdominal surgery, and BL13 may benefit the respiratory system. ST36 is located on the anterior aspect of the leg, at 3 *cun* (Chinese inch) below the kneecap and 1 *cun* from the anterior crest of the tibia. BL13 is located at 1.5 *cun* lateral to the spinous process of the third thoracic vertebrae. One *cun* is defined as the width of the patient’s thumb (see supplementary material 2). The patients in the DT and ST groups receive electrical stimulation with the “disperse-dense” waves of alternating frequencies of 2 and 15 Hz for a 2-s cycle. Increasing electrical stimulation intensity (7–11 mA) will be applied to identify the threshold intensity, defined as perception of the “*Teh Chi*” sensations of heaviness, numbness, and swelling in their crura. Electric stimulation is administered 30 min prior to surgery and continued until the end of the surgery. Patients in the Control group receive the same treatment without electric stimulation.

#### Blinding

All patients will never have been subjected to transcutaneous electrical stimulation treatment before. Patients were told that they may or may not be able to feel the electrical stimulation. The skin surface was sterilized by alcohol and electrodes were pasted to bilateral ST36 and BL13. The generator was connected by leads to two sterile electrodes with a pre-gelled contact surface (approximately 1.5 in. × 1.5 in.) by a specific investigator who is not involved in anesthesia and follow-up. Treatment assignments were concealed from patients, data collector, research staff, the statistician, and the Data and Safety Monitoring Committee. The stimulator is placed in an opaque box to keep the surgical team and the anesthetists blinded to group allocation. The patients and the staff on the wards are not informed during follow-up about the intervention received. An independent Data and Safety Monitoring Committee oversees the study conduct and reviews the blinded safety data. Unmasking will be done when a severe adverse event happens. The Committee consists of a surgeon, an intensive care unit (ICU) physician and an anesthesiologist who is not involved in the study. The members of the Steering Committee vouch for the accuracy and completeness of the data and analyses and the fidelity of the study to the protocol.

At the end of the follow-up, to evaluate participant blinding, the patients are asked which of the groups they believed they belonged to and to give a reason for their choice. No investigator has access to patient allocation and outcome data at the same time. All statistical analyses are performed with the intervention groups named A, B, and C, and the statistician is blinded to allocation.

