We focus on a specific population though this trial is a pragmatic design. First, we exclude patients with severe comorbidities because, in these patients, the postoperative complications could be so severe that protection by TEAS will be too weak to be observed. Second, we exclude patients with contraindications to electrical stimulation, to ensure that TEAS would not do harm to these patients.

Based on TCM theory, the onset of acupuncture’s effect is 15–30 min, and acupuncture during anesthesia may be not comparable to that in conscious patients. Previous studies in which acupuncture was started after the induction of anesthesia revealed reduced efficacy or a lack of efficacy, although the mechanism underlying this phenomenon is not known [15, 16]. So in our study we will start the TEAS at 30 min before anesthesia induction.

Considering that among the postoperative complications, pulmonary complications are closely related to general anesthesia, we choose the incidence of pulmonary complications as primary outcome. Atelectasis develops within minutes after the induction of general anesthesia [4] and age is a risk factor for pulmonary complications. Age-related changes in pulmonary function [17] may increase the possibility of intraoperative lung injury. Almost all mechanically ventilated elderly patients developed atelectasis and shunt during anesthesia [5].

A limitation of this study is the validity of blinding, since interventions will begin when the participants are awake. To solve the problem, for all participants, we attached electrodes to all acupoints and the patients are told that they may or may not feel the stimulation. At the end of the follow-up, to evaluate participant blinding, the patients also are asked which of the groups they believed they belonged to and to give a reason for their choice. By these manipulations, we hope to blind the participants.

In conclusion, the results of this trial are expected to confirm whether this acupuncture-related technique is effective in decreasing postoperative complications in elderly patients.

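### Patient blinding for TEAS versus Control is not credible by design: current is raised to a felt sensation in awake TEAS patients, while Control patients receive none

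*Protocol article*

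**What the plan says.** All quotations are from the protocol article.

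- **Dose setting in the TEAS arms** (Rationale for acupuncture protocol): "Increasing electrical stimulation intensity (7–11 mA) will be applied to identify the threshold intensity, defined as perception of the" response that the section calls *Teh Chi*. It describes this response as "sensations of heaviness, numbness, and swelling in their crura".
- **Control arm** (same section): "For the Control group, electrodes are attached but no stimulation is given", and "Patients in the Control group receive the same treatment without electric stimulation".
- **Concealment claim** (Blinding): "Treatment assignments were concealed from patients, data collector, research staff, the statistician, and the Data and Safety Monitoring Committee". The sentence carries no qualification.
- **Masking devices** (Blinding): electrodes at both sites in every patient, patients new to transcutaneous stimulation, and the script "Patients were told that they may or may not be able to feel the electrical stimulation".
- **Blinding check** (Blinding): at the end of follow-up, patients are asked which group they think they were in, and why. The Design section puts the end of follow-up at 1 year.
- **Admission** (Discussion): the validity of blinding is called a limitation because the intervention begins in awake patients. The electrodes and the script are offered as the solution, and the paragraph ends "By these manipulations, we hope to blind the participants".

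**The concern.** The script can mask only if a patient in an active arm might plausibly feel nothing. The dosing rule removes that possibility as far as it can, because feeling the stimulation is the criterion by which the intensity is chosen. The concealment sentence and the dosing rule therefore conflict for TEAS versus Control.

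That contrast matters most. The Discussion gives the effectiveness of TEAS in reducing complications as the trial's primary consideration. Patients who know that they are treated may report or behave differently, and may tell the ward staff, who are protected only by not being informed. If some endpoint items depend on the patient, part of an observed difference could come from that knowledge and be credited to TEAS, in a trial described as concealing assignment from its patients.

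**Working it through.** The point rests on comparing sections. The plan states no figure on blinding that could be reproduced.

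**Step 1: what a patient can perceive, by arm**

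| Arm | Planned n | Current at ST36 | Current at BL13 | Sensation expected under the dosing rule |
|---|---|---|---|---|
| Dual-acupoint (DT) | 115 | yes | yes | leg sensation, used to set intensity |
| Single-acupoint (ST) | 115 | yes | no | leg sensation, used to set intensity |
| Control | 115 | no | no | none from current |

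Titrated to sensation: 115 + 115 = 230 of 345. No current: 115 of 345. Setting a threshold by perception presupposes an awake patient, and the Discussion says that the intervention begins in awake patients.

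**Step 2: what each masking device can do**

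- *Electrodes at all sites* hide which sites were chosen. They do not hide whether current flows.
- *Patients new to the technique* cannot compare the sensation with an earlier one. Noticing heaviness, numbness and swelling needs no earlier experience.
- *The script* gives a Control patient a reason to think that unfelt stimulation is possible. It gives a TEAS patient who feels the current no reason for doubt.

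The masking is therefore one-sided: weak in the TEAS arms and possibly effective in Control.

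**Step 3: DT versus ST**

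The threshold is defined by sensation in the legs, which both TEAS arms share. The article does not say that patients know how many sites should be active. Nothing stated shows that DT and ST patients can tell their arms apart.

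**Step 4: what a bias would do (illustration only)**

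Inputs from Sample size calculation and statistical analysis: Control rate 32%, n = 115 per arm, two-sided 5% level. Assumption of this review, not of the documents: no true effect, and knowledge of treatment lowers the recorded rate in both TEAS arms by b.

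The three rates are 0.32, 0.32 − b and 0.32 − b, with mean p̄ = 0.32 − 2b/3. The squared deviations from p̄ sum to (2b/3)² + 2(b/3)² = 2b²/3. The non-centrality of the overall χ² test (2 df) is

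λ = 115 × (2b²/3) / [p̄(1 − p̄)].

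| b | p̄ | p̄(1 − p̄) | λ | P(reject at 5%) |
|---|---|---|---|---|
| 0.03 | 0.300 | 0.2100 | 0.329 | 7.6% |
| 0.05 | 0.287 | 0.2045 | 0.937 | 12.7% |
| 0.08 | 0.267 | 0.1956 | 2.509 | 27.4% |

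For scale, the planned step between neighbouring arms is 9 points (32% to 23% to 14%). The 8-point case requires knowledge of allocation to remove 0.08/0.32 = 25% of recorded complications in both TEAS arms.

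**The case against.** The strongest reply is that the authors already disclose the problem. The Discussion names its cause, ends on a hope and not an assertion, and the plan collects patients' guesses with reasons. This stands in part: the limitation is not hidden. But the Blinding section still asserts concealment outright, and the Discussion presents as a remedy two devices that do not work on a patient who feels current. The guess is asked only at the end of the 1-year follow-up, so it can reflect recall and outcome as well as what was felt.

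Several stronger readings are tempting, and the documents do not support them:

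- *That the blinding claim is simply false, because feeling means TEAS and not feeling means Control.* Patients are not told their group. Control patients who are new to the technique and have been told that they may feel nothing can stay unsure. It is also an inference that every TEAS patient feels the current: the article gives a range of 7–11 mA and does not say what happens if nothing is felt within it.
- *That the silent BL13 site unmasks ST against DT.* This is not shown, for the reason in step 3 of the working.
- *That the endpoint is known to rest on patient-reported symptoms.* Operative details mentions recording symptoms next to the end-of-surgery checklist and does not tie this to 30-day scoring. The items are in supplementary material 3, which is not shown here. What is visible points partly the other way: imaging is read by a radiologist unaware of the intervention, and a qualifying event needs two grade-2 items or one grade-3 or grade-4 item.
- *That the trial has an inflated error rate of 7.6% to 27.4%.* The biases behind those figures are assumptions with no basis in the documents.

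Finally, the surgical team, anesthetists, radiologist and statistician have their own masking arrangements, and a patient who feels current does not by that fact unblind them.

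**Conclusion.** The point holds for TEAS versus Control. The dosing rule undermines the unqualified statement that assignment is concealed from patients. Patient blinding for this contrast is not credible by design: TEAS patients will generally know that they are stimulated, and Control patients may not know that they are not.

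The conclusion rests on the stated titration to perception, the zero-current Control and the awake patient, all of which the article gives. It does not depend on any assumed bias. How much bias follows cannot be determined, because the number of endpoint items that depend on patient report is unknown. This should be corrected because it limits how a TEAS-versus-Control difference may be described. It does not show that the result will be biased.

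**What to change.** 1. **Correct the claim.** In Blinding and in the limitation paragraph of the Discussion, withdraw the unqualified statement of concealment from patients for TEAS versus Control. State instead that patients are not told their group, that those receiving TEAS are likely to recognise stimulation, and that masking of ward staff and data collectors depends on patients not disclosing it. Relabelling the trial as assessor-blinded would claim more than is secured.

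2. **Add one supportive analysis.** Pre-specify the TEAS-versus-Control comparison on components that do not rest on patient report, such as infiltrates or atelectasis read by the blinded radiologist. Choose the components from supplementary material 3 before unblinding. Report the estimate with its 95% CI beside the primary result, without a pass/fail rule: there will be fewer events, and the article offers no basis for a criterion of agreement.

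Both can be done with recruitment under way (113 of 345 at submission). Neither changes the intervention, and the analysis uses data already planned for collection. The cost is a less favourable blinding statement and a wider interval in the supportive analysis.

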Interim analyses are performed after half the required participants had been enrolled (*n* = 173). If the Institutional Review Board thought it was no longer ethical to withhold TEAS from the patients in the non-acupoint and Control groups based on the results of the interim analysis with pulmonary complications as the endpoint, the study will be stopped.

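### The safety committee is denied the allocation key, and the only stated stopping criterion asks about benefit and goes to another body, so no stated route turns a by-arm safety signal into action on harm

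*Protocol article*

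**What the plan says.** The Blinding section of the protocol article makes four relevant statements.

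- On who is masked: "Treatment assignments were concealed from patients, data collector, research staff, the statistician, and the Data and Safety Monitoring Committee".
- On the Committee's task: "An independent Data and Safety Monitoring Committee oversees the study conduct and reviews the blinded safety data".
- On exceptions: "Unmasking will be done when a severe adverse event happens". It does not say who learns the assignment, or whether events are then compared between arms.
- On coding: "All statistical analyses are performed with the intervention groups named A, B, and C, and the statistician is blinded to allocation".

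The interim paragraph that closes the section on sample size and statistical analysis sets the timing: "Interim analyses are performed after half the required participants had been enrolled", given there as n = 173. It then states the only stopping criterion in the article, which opens with this condition: "If the Institutional Review Board thought it was no longer ethical to withhold TEAS from the patients in the non-acupoint and Control groups". The evidence for that judgement is the interim comparison of pulmonary complications, and the consequence is that the trial ends. The Committee is not mentioned in that paragraph.

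**The concern.** A monitoring committee protects participants by comparing arms. Here the body charged with safety is, by a stated rule, kept from knowing which arm is which. The one review for which the article states a stopping consequence is given to a different body. That review asks a single question, in the direction of benefit, on a single endpoint. Deaths and ICU admissions, both secondary outcomes under Outcome measurement, are not named in it.

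The participants are surgical patients aged 65 or older. Under 1:1:1 allocation two thirds of them, 230 of 345, receive TEAS. If DT or ST did worse than Control, the article would give the Committee no means of attributing the excess to an arm, and it would give the Board no stated criterion to apply to it.

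**Working it through.** No figure in the plan is in dispute. The point turns on reading the two sections together. The arithmetic only shows what a Committee without the key could and could not see.

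**Inputs from the article.** Planning rates for pulmonary complications: Control 32%, ST 23%, DT 14%. Total 345, allocated 1:1:1. Interim at 173, which agrees with 345/2 = 172.5.

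**Step 1: expected benefit at the interim.** Per arm 173/3 = 57.7. This assumes that all 173 have known 30-day outcomes.
- Pooled rate: (0.32 + 0.23 + 0.14)/3 = 0.23.
- Total events: 173 × 0.23 = 39.8.
- By arm (Control/ST/DT): 57.7 × 0.32 = 18.5; 57.7 × 0.23 = 13.3; 57.7 × 0.14 = 8.1.

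**Step 2: mirror-image harm.** Assumed for illustration: Control 14%, ST 23%, DT 32%. The pooled rate is again 0.23 and the total again 39.8. By arm: 8.1, 13.3, 18.5.

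**Step 3: what each form of review shows.**

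| Form of review | Expected benefit | Mirror-image harm | Told apart? |
|---|---|---|---|
| Pooled | about 40 events | about 40 events | No |
| Coded A/B/C, no key | counts of about 18, 13 and 8 in unknown order | the same three counts | Imbalance seen, direction not |
| Coded, key available | 18/13/8 | 8/13/18 | Yes |

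**Step 4: harm that is not a mirror image** (rates assumed, not from the article).
- If DT had 50% with the other arms as planned, the pooled rate would be (32 + 23 + 50)/3 = 35% against 23% planned. The standard error at 173 is √(0.23 × 0.77/173) = 0.032, so z = (0.35 − 0.23)/0.032 = 3.75. A pooled excess of that size would be noticed, but a background rate higher than planned in every arm could explain it equally well.
- For a rarer serious event at 2%, 2% and 10%, the pooled rate is (2 + 2 + 10)/3 = 4.7%. That is 173 × 0.047 = 8.1 events, against 173 × 0.02 = 3.5 if all arms were at 2%.

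**Step 5: limits of the remedy.** By-arm data are not powerful at this size either. With 58 per arm and two-sided 0.05, power is about 50% for 32% against 50%, and about 44% for 2% against 10%. What the key adds is direction and attribution, not certainty.

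**Step 6: the passages side by side.** Concealment from the Committee is unqualified. Unmasking at a severe adverse event would break it if the Committee is the body told, and would not inform the Committee if it is not. The text leaves both readings open. Under Outcome measurement, a primary event can arise from two grade-2 items, and the article does not say that such an event, or an ICU admission, counts as a severe adverse event.

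**The case against.** A reader might infer that harm in a TEAS arm could not be detected or acted on at all. The documents do not support that, for four reasons.

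- The Board cannot judge whether withholding TEAS is still ethical without results by identified group. At n = 173 it would therefore see the direction of any difference in pulmonary complications. The counts in Step 3 describe the Committee's view, not everyone's.
- It is tempting to read blinded as pooled, but the article never says pooled. Its analyses are coded by arm, so the Committee's tables may be too, and an imbalance would then be visible.
- Unmasking at a severe adverse event links at least some events to an arm. If every such unmasking reached the Committee, it could keep a tally.
- A Committee that oversees conduct is not barred from recommending a pause merely because no harm criterion is written down. A charter or full protocol, not shown here, may hold review tables and guidance on harm.

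All four stand, and they limit the point. They do not remove it. Coding without the key still hides direction. The unmasking sentence names no recipient and sits unreconciled beside the concealment. The Board's look covers one endpoint, with a criterion in one direction only. Concealment from the Committee and the benefit-only criterion are rules the article states, not details it leaves to another document. The mirror-image rates are a device for illustration; nothing in the article suggests that TEAS is harmful.

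**Conclusion.** The point holds in a limited form. As written, the Committee reviews safety data without the key, so it cannot tell whether an imbalance between arms is for or against TEAS. The only stated stopping criterion runs towards benefit, rests on pulmonary complications alone, and lies with the Institutional Review Board with no stated Committee role. Unmasking at a severe adverse event fills the gap only in part and conflicts on its face with the concealment.

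The size is structural, not a bias in the final estimate: two scenarios that differ by 18 percentage points between DT and Control in opposite directions look identical to the Committee. This rests on reading concealment of assignments as withholding the key, which is what the text says, and on no unseen document overriding it. The change should be made. It does not undermine the trial's validity, and it is not evidence that harm would go unseen by everyone.

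**What to change.** **Blinding section.** Take the Committee out of the list of those masked to group-level data. State that in closed session it reviews deaths, severe adverse events, ICU admissions and primary events tabulated by arm, coded A/B/C. The key should be available on request from the holder of the randomization system, outside the masked team. Reconcile the unmasking sentence with this by saying who is told the assignment after a severe adverse event and whether the Committee receives it.

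**Interim paragraph.** Send the interim results to the Committee and state its role alongside the Board's. Make the review two-directional, so that the Committee can recommend a pause or stop for an excess of events in DT or ST as well as for benefit.

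**Cost.** Some protocol wording, one closed table per review, and a key-handling step that must stay outside the masked team. Patients, clinicians, assessors and the trial statistician remain masked. Trial status reports 113 recruited at submission, 173 − 113 = 60 short of the interim, so at that date the change could still have been in place before the interim look.
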